### 11.3 SAMPLE SIZE DETERMINATION AND PLANNED RECRUITMENT RATES

Due to nature of this study (proof of concept phase II trial), with effect size being unknown, following assumptions were made:

- Proportion of subjects randomized to receive IMP achieving primary endpoint will be 40% and this proportion will be identical in a placebo group
  - A non-inferiority margin  $\delta$  will be equal to 15%
  - One sided significance level 0.2
  - Power of 70%
  - One interim analysis (with Hwang-Shih-DeCani  $\alpha$  pending function)
  - A drop-out rate of 10%.
- Taking these into consideration, a minimal number of subjects per group is 46 – so 92 subjects in each study arm.

Sample size calculations were made in R version 3.6 using gsDesign library version 3.1.1.

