## 11.5 STATISTICAL ANALYSES

### 11.5.1 GENERAL ASSUMPTIONS

#### 11.5.1.1 STATISTICAL SIGNIFICANCE ASSUMPTIONS

Statistical significance level will be equal to 0.20 for purpose of primary endpoint analysis and 0.05 otherwise. P values  $\geq 0.001$  will be reported to 3 decimal places; p-values less than 0.001 will be reported as “<0.001”. The mean, standard deviation, and any other statistics other than quantiles, will be reported to one decimal place greater than the original data. Quantiles, such as median, or minimum and maximum will use the same number of decimal places as the original data. Estimated parameters, not on the same scale as raw observations (e.g. regression coefficients) will be reported to 3 significant figures.

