### 11.5.2.1 ANALYSIS OF THE PRIMARY ENDPOINT

Primary endpoint analysis for each study arm (dabigatran, apixaban, or rivaroxaban) will be performed independently. Proportion of subjects achieving primary endpoint for active treatment and placebo as well as difference of proportions together with 82% Confidence Interval (CI) will be calculated. One-sided noninferiority test with 15% margin for difference in proportions will be performed. A p value lower than 0.176 will be considered as statistically significant.

---

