#### 11.5.4.1 INTERIM ANALYSIS OF EFFICACY AND SAFETY ENDPOINTS

An interim analysis is planned after half of the randomized subjects reach primary endpoint (functional status assessment with modified Rankin scale on day 90). All collected data will be analysed. Primary endpoint will be tested using one sided  $\alpha=0.0238$ .

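### The primary decision rule is inconsistent: the final threshold is repeated under the interim heading, the 82% CI does not match it if two-sided, and 0.176 is leftover alpha, not a boundary

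*Protocol*

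**What the plan says.** - **Design (Protocol 1.1.9.1 and 11.3).** "One sided significance level 0.2", 70% power, a 15-point margin, 10% drop-out, and one interim with Hwang-Shih-DeCani spending. The gamma parameter is not given. The minimum is 46 per group.
- **General level (11.5.1.1).** "Statistical significance level will be equal to 0.20 for purpose of primary endpoint analysis and 0.05 otherwise".
- **Final analysis (11.5.2.1).** "One-sided noninferiority test with 15% margin for difference in proportions will be performed". The decision is then: "A p value lower than 0.176 will be considered as statistically significant". For estimation, "difference of proportions together with 82% Confidence Interval (CI) will be calculated". Whether this interval is one-sided or two-sided is not stated.
- **Interim heading (11.5.4).** The paragraph from 11.5.2.1 appears again word for word, including 0.176 and the 82% interval.
- **Interim subsection (11.5.4.1).** The look comes when half of the randomised subjects have reached day 90. "Primary endpoint will be tested using one sided" alpha of 0.0238.

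Each NOAC arm is analysed separately and has its own interim (1.1.10.1), so the rule applies three times.

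**The concern.** These statements cannot all be followed. The interim has two thresholds, 0.0238 and 0.176, and the looser one breaks the stated error rate. At the final look, the p-value rule and the interval printed beside it can point in opposite directions if the interval is read in the usual two-sided way. And 0.176 looks like a subtraction result used as a critical value. At stake is whether an arm can be declared non-inferior, and at what error rate. The IDMC sees efficacy data at the interim (11.5.4.3), so the rule has to be unambiguous before then.

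**Working it through.** **Inputs.** From 11.3: one-sided alpha 0.20, power 70%, 40% response in both groups, margin 15 points, drop-out 10%, 46 per group. From 11.5.4.1: interim at half information, level 0.0238. From 11.5.2.1: final cut-off 0.176 and an 82% interval. Assumed: gamma = -4.

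**1. Reproducing the plan's figures.**
- Spend at half information: 0.2 × (1 - e^2)/(1 - e^4) = 0.02384. Of gamma = -8, -4, -2, 0 and 1, only -4 gives 0.0238.
- Remainder: 0.2 - 0.02384 = 0.1762. This is where 0.176 comes from.
- Fixed sample size: 0.48 × (0.8416 + 0.5244)²/0.15² = 39.8. Times the group-sequential inflation of 1.006 this is 40.05, rounded up to 41; 41/0.9 = 45.6, rounded up to 46. The sample size reproduces and is not in dispute.

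**2. The final boundary.** The two test statistics have correlation √0.5 = 0.707. The final critical value c solves

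1 - P(Z1 < 1.980, Z2 < c) = 0.20,

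which gives c = 0.853, a nominal one-sided p of 0.197. The spend of 0.176 is the probability of crossing at the final look without having crossed at the interim. It is smaller than the nominal level because some trials that would cross at the end have already crossed at the interim.

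**3. Error rate and power of each rule** (same integral; power uses SE = √(0.48/n) with n = 41 to 41.4 evaluable per group, since 46 × 0.9 = 41.4).

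| Interim p | Final p | Overall one-sided alpha | Power |
|---|---|---|---|
| 0.0238 | 0.197 | 0.200 | 70.6–70.8% |
| 0.0238 | 0.176 | 0.180 | 67.9–68.1% |
| 0.176 | 0.176 | 0.255 | 73.4–73.6% |

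**4. Interval against test.**
- Two-sided 82%: one-sided level (1 - 0.82)/2 = 0.09, about half of 0.176.
- Two-sided interval matching 0.176: 1 - 2 × 0.176 = 64.8% (one-sided bound 82.4%).
- Two-sided interval matching 0.197: 1 - 2 × 0.1967 = 60.7% (one-sided bound 80.3%).
- Two-sided interval matching 0.0238: 1 - 2 × 0.0238 = 95.2%.

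Example: 15/41 on active and 16/41 on placebo. The difference is -2.4 points, SE 10.7 points, z = (-0.0244 + 0.15)/0.1071 = 1.173, p = 0.120. That passes p<0.176. The two-sided 82% lower limit is -0.0244 - 1.341 × 0.1071 = -16.8 points, which crosses -15.

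Exact binomial enumeration (41 per group, 40% in both, Wald statistic) puts the chance of p<0.176 with the two-sided 82% limit beyond -15 points at 14.4%.

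**The case against.** **The pair 0.0238 and 0.176 is a legitimate rule.** The two sum to 0.1998, a Bonferroni-type split of 0.20, and actual error is 0.180. This stands. A reader might infer that 0.176 inflates the error rate or invalidates the final test. It does neither; it costs roughly 2.6 points of power.

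**Section 11.5.4.1 is the specific text and already has the right interim level.** The paragraph above it looks like a copy. That is the likeliest reading, so 0.255 is what follows if 11.5.4 is taken literally, not the error rate the trial is bound to have. The copied text still stands under the interim heading and still contradicts the subsection.

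**The protocol decides by p-value; the interval is only to be calculated.** This stands. A reader might infer that the trial has only about 53% power, the figure obtained if the final decision rested on the two-sided 82% limit. No section sets that rule.

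**The 82% may be meant as one-sided, 1 - 0.176 rounded.** Possible. In the example the one-sided bound is -12.2 points and agrees with the p-value, and significant results with a bound beyond the margin no longer occur. But sidedness is not stated, and an interval for a difference is normally read as two-sided.

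**The 0.20 in 11.5.1.1 is the overall budget.** That is the natural reading, and it is not a further conflicting threshold. It only needs a label.

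**Moving to 0.197 loosens the success criterion.** Version 4.0 is dated December 2022 and first enrolment was planned for 4Q2021, so this deserves weight. It is why keeping 0.176 has to remain an open choice.

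**Conclusion.** The primary decision rule is inconsistent as written, in three respects of unequal weight.

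1. The interim thresholds in 11.5.4 and 11.5.4.1 contradict each other. This is the most serious, because the looser one would take overall alpha to 0.255.
2. The 82% interval does not match p<0.176 under the usual two-sided reading, with about 14% disagreement when both groups respond at 40%. If one-sided was meant, the defect is only that the protocol does not say so.
3. The 0.176 is an alpha increment and not the nominal boundary, which is 0.197. The consequence is conservatism: alpha 0.180 and power about 68%, against the stated 0.20 and 70%.

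The results rest on gamma = -4 (inferred, not printed), an interim at exactly half information, the normal approximation for alpha and power, and 41 to 41.4 evaluable per group.

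**What to change.** All changes are wording, with no added patients, and should be made before any unblinded interim.

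- **11.5.4:** replace the repeated paragraph with the interim rule, one-sided p<0.0238, and its matching two-sided 95.2% interval.
- **11.5.2.1:** choose one option and state it.
  - Final boundary p<0.197, recomputed at the actual information fraction, with a two-sided 60.7% interval or a one-sided 80.3% bound.
  - Or knowingly keep p<0.176, with a two-sided 64.8% interval or a one-sided 82.4% bound, and restate overall alpha as 0.18 and power as about 68%.
- **Interval:** say in each place whether it is one-sided or two-sided.
- **11.5.1.1:** label 0.20 as the overall one-sided level across both looks.
- **11.3:** print the gamma value used, so that the boundaries can be checked.

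The first option loosens the final criterion and regains the planned power. The second leaves the criterion unchanged and accepts about 2.6 points less power.

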### 11.5.2.2 ANALYSIS OF THE SECONDARY ENDPOINT(S)

For each study arm (A, B or C) proportion of subjects randomized to placebo and active treatment and proportion difference together with 95% CI will be presented. Unadjusted and adjusted (with subject age) odds ratios will be shown. P value lower than 0.05 will be considered as statistically significant ( $\alpha=0.05$ ).

---

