| To assess the efficacy of the investigational therapy in patients with acute ischaemic stroke on the non-vitamin K antagonist oral anticoagulants compared to placebo using NIHSS score.                                                                        | Change in NIHSS score from baseline assessed at 7 (+/-1 day), and 90 days (+/- 3 days) after investigational treatment administration.                                                                                                              |
| Safety                                                                                                                                                                                                                                                   |                                                                                                                                                                                                                                                     |
| To assess the incidence of fatal events after the investigational therapy in patients with acute ischaemic stroke on the non-vitamin K antagonist oral anticoagulants compared to placebo.                                                                      | Incidence of deaths:
- Deaths from any cause
- Deaths subdivided by cause
at 7 (+/-1 day), 30 (+/-2 days) and 90 days (+/- 3 days) after investigational treatment administration.                                                         |
| To assess the incidence of non-fatal events after the investigational therapy in patients with acute ischaemic stroke on the non-vitamin K antagonist oral anticoagulants compared to placebo.                                                                  | Incidence of non-fatal events defined as
- Recurrent ischaemic stroke
- Haemorrhagic stroke (ICH or SAH)
- Neurological deterioration (NIHSS)
at 7 (+/-1 day), and 90 days (+/- 3 days) after investigational treatment administration. |

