Eligible patients allocated to each study group will be randomised at 1:1 ratio to receive experimental treatment or corresponding placebo (see section 6.4). Study treatment is composed of sequential intravenous administration of NOAC-specific antidote (or placebo) followed by the infusion of rtPA or corresponding placebo.

Standard diagnostic procedures, allocation to the study group and randomisation should be completed within 3.0 hrs from AIS symptoms onset to minimise the risk of delay to start of the study treatment. Randomisation scheme will include severity of the IS at randomisation (<6 points, and  $\geq 6$  points in NIHSS) as a stratification factor in all 3 study groups (arms).

Administration of rtPA should be initiated within 4.5h time window calculated from the onset of AIS symptoms but no later than 6h in specific circumstances (correctly performed randomisation process and administration of the antidote, unavoidable factors delaying administration of rtPA beyond 4.5 hours).

After receiving study treatment patients will be assessed at 24 (+/-4) hrs (Visit 2), 7 (+/-1) days (Visit 3), 30 (+/-2) days (Visit 4), and 90 (+/-3) days after rtPA bolus treatment administration and collected data will be recorded in the eCRF (please see Schedule of Assessments [SoA] in [Section 1.3](#))

An Independent Data Monitoring Committee (IDMC) will be established before the start patients' enrolment to monitor progress of the clinical study and to ensure participants' safety. This will include reviewing unblinded safety and the efficacy data, estimating the benefit-risk balance during the study and supervising the overall conduct of the study.

The composition and responsibilities of the IDMC will be described in the IDMC charter.

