## 6.4 RANDOMISATION

Subjects allocated to A, B, or C study group (arm), defined by NOAC taken before AIS onset (see [Section 4.1](#)), will be randomized in 1:1 ratio to receive either active treatment or placebo (comparator).

A stratified variable block length randomization based on a computer-generated randomization schedule integrated into the eCRF software will be used (see [Section 7.3.1](#)).

Stratification will consider severity of the IS at randomization (<6 points in NIHSS, and ≥6 points in NIHSS).

---

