## 9 STUDY ASSESSMENTS AND PROCEDURES

### 9.1 EFFICACY ASSESSMENTS

#### 9.1.1 NATIONAL INSTITUTES OF HEALTH STROKE SCALE (NIHSS)

The National Institutes of Health Stroke Scale (NIHSS) is a systematic assessment tool that provides a quantitative measure of stroke-related neurologic deficit, and is valid for predicting lesion size and can serve as a measure of stroke severity; the NIHSS has been shown to be a predictor of both short and long term outcome of stroke patient.

The NIHSS will be used as a clinical stroke assessment tool to evaluate and document neurological status in acute stroke patients in the STROACT study. Stroke severity according to NIHSS scores will be stratified as follows:

- Very Severe: >25
- Severe: 15 – 24
- Mild to Moderately Severe: 6 – 14
- Mild: 1 – 5

NIHSS score (<6 points in NIHSS, and  $\geq 6$  points in NIHSS) will be the stratification factor used in randomisation.

NIHSS assessment form is included as Appendix in [Section 14.1.1](#).

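### Randomisation is stratified by NIHSS, but the adjusted secondary and safety models use age only, the primary test names no strata, and the NIHSS-change endpoint has no usable method

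*Protocol*

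**What the plan says.** Allocation is 1:1 within each anticoagulant arm. Section 6.4 states: "Stratification will consider severity of the IS at randomization", with cut-point NIHSS below 6 against 6 or more. Section 4.1 confirms that severity enters "as a stratification factor in all 3 study groups (arms"). Section 9.1.1 says of the same scale that "the NIHSS has been shown to be a predictor of both short and long term outcome of stroke patient".

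The analysis sections do not carry the factor forward:

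- **Primary (11.5.2.1, repeated in 11.5.4).** "Primary endpoint analysis for each study arm (dabigatran, apixaban, or rivaroxaban) will be performed independently". Then: "One-sided noninferiority test with 15% margin for difference in proportions will be performed". The threshold is also fixed: "A p value lower than 0.176 will be considered as statistically significant". No stratum, covariate, test statistic or variance is named.
- **Secondary (11.5.2.2).** Proportions, their difference with a 95% CI, and: "Unadjusted and adjusted (with subject age) odds ratios will be shown".
- **Key safety (11.5.2.5).** Haemorrhages, deaths, recurrent strokes and neurological deterioration follow the secondary method.

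Section 3.2 lists two secondary efficacy endpoints. One is binary (mRS 0-1). The other is "Change in NIHSS score from baseline assessed at 7 (+/-1 day), and 90 days (+/- 3 days) after investigational treatment administration".

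**The concern.** When randomisation is stratified on a prognostic factor, an analysis that leaves the factor out uses a standard error that is too large, because it counts between-stratum variation that the design has already balanced. The result is a wider interval, a true error below the nominal one, and some lost power. For odds ratios, omitting a prognostic factor also pulls the estimate towards 1 relative to the within-stratum odds ratio. Section 11.5.2.2 chooses one covariate, and it is not the one the design was built on.

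The second problem needs no assumption about effect size. Change in NIHSS is a score. No responder definition is given, so the method of the only section on secondary efficacy endpoints cannot produce a result for it. Section 11.5.2.3 meanwhile gives Barthel, MoCA, HADS and BNP, which rank lower, an ANCOVA on baseline with a rank-based fallback.

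**Working it through.** **Reproducing the plan's figures (section 11.3).** Inputs: 40% in both groups, margin 15 points, one-sided 0.20, power 70%, drop-out 10%.

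- n = 2 x 0.4 x 0.6 x (0.842 + 0.524)^2 / 0.15^2 = 39.8, so 40 per group; 40/0.9 = 44.4, so 45.
- With one Hwang-Shih-DeCani interim (gamma -4, inferred because it reproduces the stated interim alpha): 40.05/0.9 = 44.5, so 45. Adding a futility bound gives 45.1 or 47.0, depending on its spending parameter. The stated 46 is within two patients.
- Interim alpha: 0.2 x (1 - e^2)/(1 - e^4) = 0.0238, as stated.

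All of these are unstratified calculations.

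**Primary test.** Section 11.4.2 makes patients with a day-90 mRS the main efficacy set, so the evaluable number is 46 x 0.9 = 41.4 per group. The one-sided critical value for 0.176 is 0.931. Stratum rates and mix are assumptions, chosen to average the planned 40%.

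- Crude variance per patient: 0.4 x 0.6 = 0.24.
- Within-stratum variance v: weighted mean of p(1 - p). For 60%/20% in equal strata, 0.5 x 0.24 + 0.5 x 0.16 = 0.20.
- SE = sqrt(2 x variance / 41.4). For 60%/20%: crude 10.8 points, stratified 9.8.
- True level of the crude test = 1 - Phi(0.931 x sqrt(0.24/v)).
- Power at equal rates = 1 - Phi((0.931 x SE used - 0.15) / stratified SE).

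| Assumed rates (mix) | v | Variance change | True level, crude | Power, crude | Power, stratified |
|---|---|---|---|---|---|
| 50/30 (50:50) | 0.2300 | -4% | 0.171 | 68.2% | 68.9% |
| 55/25 (50:50) | 0.2175 | -9% | 0.164 | 68.6% | 70.3% |
| 60/20 (50:50) | 0.2000 | -17% | 0.154 | 69.4% | 72.4% |
| 70/20 (40:60) | 0.1800 | -25% | 0.141 | 70.3% | 75.1% |

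The gain runs from 0.7 to 4.8 points. At a weaker contrast of 45/35 it is about 0.2. If all 46 per group were evaluable, the crude test would reach 70.6% to 72.2% over contrasts from 45/35 to 60/20.

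**Small-sample caution.** These are normal approximations. In simulations of binomial counts at 60/20 with 23 patients per stratum and group, a plain stratified Wald test had a true level of about 0.19 against 0.176; the crude test had 0.141. At 50/30 with 41 per group the two levels were 0.185 and 0.184. Discreteness therefore moves the level about as much as stratification does. In a check of the 60/20 setting, the stratified Miettinen-Nurminen statistic lay only slightly below the Wald one and still above 0.176.

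**Secondary odds ratios.** Simulated at 46 per group, equal strata, two-sided 0.05, crude chi-square against the Cochran-Mantel-Haenszel (CMH) test, 200,000 trials, age not modelled:

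| Placebo rates | Type I, crude / CMH | Power at within-stratum OR 2.5, crude / CMH | OR with NIHSS omitted |
|---|---|---|---|
| 50/30 | 0.042 / 0.048 | 54.0% / 55.5% | 2.40 |
| 60/20 | 0.029 / 0.050 | 41.9% / 50.7% | 2.13 |

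**Sparse safety events.** At the 3-7% symptomatic intracranial haemorrhage rate in section 2.3.1, 46 patients yield 1.4 to 3.2 events (46 x 0.03, 46 x 0.07).

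**Stratum definition.** Sections 1.1.2, 4.1, 6.4 and 9.1.1 put a score of 6 in the upper stratum. Section 7.3.1 prints below 6 and above 6, which leaves a score of 6 in neither.

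**The case against.** The strongest reply concerns the primary test. A reader might infer that the protocol prescribes a crude test whose error rate is wrong. The text does not support that. Section 11.5.2.1 gives the effect measure, margin and threshold and is silent on the test statistic; a stratified risk-difference test would fit the same sentence. Sections 1.1.10 and 11.1.2 leave detail to a SAP that is not at hand. Leaving out the strata also errs in the safe direction, so there is no inflation to correct. This reply stands, and for the primary test the point is only a request to state what is intended.

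The sizes rest on stratum rates the protocol does not give. Eligibility narrows severity (disabling deficit required, NIHSS above 18 excluded), so a 40- or 50-point gap between strata is not established. That stands too. Nor is chance imbalance on the NIHSS stratum much of an argument, because blocked stratification already limits it.

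One could add that the age-adjusted ratios sit beside unadjusted ones in a proof-of-concept trial, and that the SAP could supply a method for NIHSS change. The first lowers the stakes but does not explain choosing age over the design factor. The second is possible, but the method the protocol does state does not fit one of the two secondary efficacy endpoints it lists.

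**Conclusion.** The point holds in a limited form. Two parts rest on fixed text: the age-only adjustment in sections 11.5.2.2 and 11.5.2.5, and a secondary-endpoint method that cannot be applied to change in NIHSS. The primary part rests on silence, which the SAP may fill.

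If the primary test is run unstratified, the cost is from under 1 to about 5 points of power at 41 evaluable per group. Crude power then lies at or a little below the planned 70%, and a stratified test recovers some or all of the shortfall. For the secondary odds ratios the simulated loss was about 1.5 to 9 points; that figure ignores age and any loss of patients, and the mRS endpoint is further restricted to patients with pre-stroke mRS 0-1. All sizes depend on the assumed strength of NIHSS as a predictor. It would be wrong to read this as a threat to the validity of the primary conclusion: omitting the strata is conservative. The improvement is worth making because it costs almost nothing.

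**What to change.** - **11.5.2.2, mRS endpoint:** add the NIHSS stratum (or baseline NIHSS) to age in the adjusted odds-ratio model.
- **11.5.2.5, safety events:** where events are sparse, use a stratified (CMH-type) or unadjusted estimate. One to three events per group cannot carry a multi-covariate logistic model.
- **NIHSS change, days 7 and 90:** ANCOVA on baseline NIHSS, or a rank version, as section 11.5.2.3 already does for other scores. Prespecify how deaths are handled. Assigning them a worst score is one option, but it is a choice of estimand and should be stated as such.
- **11.5.2.1 and 11.5.4:** state that the risk difference, its interval and the non-inferiority test are stratified by NIHSS, using a score-type method such as stratified Miettinen-Nurminen in preference to a plain Wald variance. Since discreteness remains at this size, check the true level of the chosen method by simulation before unblinding.
- **7.3.1:** align the cut-point with section 6.4, and confirm which one the eCRF randomisation uses.

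The cost is wording in the protocol or SAP. Age and NIHSS are recorded at Visit 0, so no new data, visits or patients are needed.
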